Studies have long compared rectal swabs vs bulk faeces testing. The results are varied, depending on the year the study was performed. An early study examining 700 specimens tested with MacConkey’s medium in 1940 during a Sonne dysentery outbreak (*Shigella sonnei* sp. outbreak) found that rectal swabbing was far superior to bulk faeces culture to detect an organism [8]. Rectal swabbing became the standard for a period of time This was disputed later in 1954 after a group examined 3,183 index cases looking for a variety of organisms to which they concluded that the *“…626 [bulk faeces] specimens all showed abnormalities which could be demonstrated only by microscopy or simple chemical methods, for which the rectal swab is quite unsuitable”* [9]. Since then, huge changes have occurred to our detection methods (e.g., culture media) and the advent of PCR testing for multiple organisms at once.

More recent studies demonstrate that the differences between rectal swabs and faecal samples is driven by the type of test (bacterial microscopy and culture vs viral PCR). A phase I clinical study for a live oral attenuated *Salmonella* Typhi vaccine strain found that when compared with faecal culture, rectal swabs were 64% sensitive and 90% specific [10]. A recent study on paired samples found that for bacteria, the sensitivity was 86.5% (95% CI 79.5%, 91.8%) when PCR was performed and 61.4% (95% CI 52.4%, 69.9%) when culture for bacteria was performed, indicating better performance for PCR [11].

It has been shown in small studies that rectal swabs are likely accurate. Studies have now shown that during testing for various enteric organisms (viruses and bacteria) in Rwandan children there was no significant difference in detection rate between faeces and rectal swabs for any agent, reflecting that pathogen concentration was far above the limit of detection in the majority of cases [12]. A similar paired sample study focusing on norovirus found a sensitivity of rectal swabs that was greater than 97%, and in one case detected norovirus in the swab, but not in the bulk faeces [13].

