The outcome of this project will transform clinical practice for doctors and patients. It will make testing far more convenient and allow for point-of-care testing to become a reality for enteric organisms. Currently, many people leave the emergency department without a faecal test because they could not produce a specimen while they were with the clinician. Rectal swabbing would make the diagnosis, and better care available for these patients. Public Health practitioners would be able to perform mass testing after small or large scale outbreaks, such as those caused by hepatitis A, norovirus or other organisms found in faeces [14,15]. Doctor’s in the emergency department would be able to obtain swabs on demand for testing that would expedite time spent in ED and, with the earlier diagnosis, length of stay in hospital. Most importantly, for patients, it means that they no longer must go home, wait until they need to have a bowel motion, and then return to the hospital or GP clinic with their sample, as it can be done on demand, on-site (in a private situation). Thus, rectal swabbing can transform clinical practice through earlier diagnosis, shorter length of stay’s and greatly improving the patient experience. This study aims to demonstrate that self-collected or clinician collected rectal swabs are a valid alternative method of testing when compared to bulk faeces testing for a wide range of enteric organisms such as bacterial, viral, and parasitic/protozoan. The intended outcome of this project is to replace bulk faeces testing with rectal swabbing in daily clinical and public health practice.

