### Sample size calculation

A sample size analysis with a wide range of input parameters, as described by Hajian-Tilaki 2014, demonstrates that less than 600 samples will be sufficient to cover a range of diseases (Fig 2) [16]. Assuming that 30% of samples will contain an organism (“proportion positive”) with an expected sensitivity of at least 95% (“sensitivity priors”) means we will require a sample size of no more than 61 paired samples. As the prevalence of disease in samples decreases, the sample size required is higher. For a sensitivity of 95% and a prevalence of 20%, the sample size increases from 61 to 92. These estimates are based on general sensitivity assumptions and a simplified disease prevalence model, with the literature reporting non-specific prevalence to be approximately 25%, and sensitivity estimates typically >90% [17–20]. These estimates may change slightly as recruitment progresses and the distribution of pathogens becomes clearer. To address potential variability across different pathogens, stratified analyses will be conducted. Power calculations for key pathogen subgroups indicate that, for a sensitivity of 95% (with a range of 90–99%), a minimum of 73 positive samples is required per pathogen subgroup.

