### Statistical methods

We will summarise safety and efficacy data using descriptive statistics, including means, medians, and frequencies. We will use statistical tests to compare groups (e.g., chi-square tests for categorical data, t-tests for continuous data). We will also adjust for multiple comparisons to control for type I error.

Logistic regression models will be used to assess accuracy in the presence of potential confounders. This includes sex (female/male), age (by age group), person collecting sample (self-collect/clinician collect), comorbidities, symptomatology (symptomatic/asymptomatic), duration of symptoms, and whether blood was present in the sample. Subgroup analysis will be conducted according to disease type (e.g., viral, or bacterial).

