#### Primary outcomes.

We will assess the sensitivity, specificity, positive and negative predictive value, and positive and negative agreement value, using 2x2 tables. The gold standard will be bulk faeces PCR testing. Sensitivity is the proportion of individuals with the disease who test positive with rectal swabs. We will assess the cycle threshold (CT) values using general linear models if the relationship is linear as expected and estimate the receiver operating curves and areas under the curve to assess for the potential to need differential CT value cutoffs. All results will be reported using 95% confidence intervals.

The R statistical suite will be used for all analyses and data visualisation. All estimates will be presented with 95% confidence intervals (CI). P-values <0.05 are deemed significant, and p-values <0.1 are considered trends.

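### The validity claim covers bacterial, viral and protozoan organisms, but the primary analysis is not set by organism class and the planned class-level results are not tied to the conclusion or to recruitment

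*Protocol article*

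**What the plan says.** The Introduction sets the scope of the claim: swabs are to be shown valid "for a wide range of enteric organisms such as bacterial, viral, and parasitic/protozoan". It then states the purpose: "The intended outcome of this project is to replace bulk faeces testing with rectal swabbing in daily clinical and public health practice".

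The primary analysis under Primary outcomes is "We will assess the sensitivity, specificity, positive and negative predictive value, and positive and negative agreement value, using 2x2 tables". No organism class is named there or in the Outcomes section. The margins under Interim analysis (0.35 falling to 0.10) and the 0.35 accuracy cutoff under Decision rules also name none.

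Organism type appears in two places. Statistical methods has "Subgroup analysis will be conducted according to disease type (e.g., viral, or bacterial" as its closing line, with protozoa not among the examples. Sample size calculation says "To address potential variability across different pathogens, stratified analyses will be conducted" and gives 73 positives as the minimum per pathogen subgroup. The same section says that fewer than 600 samples will cover a range of diseases.

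The Introduction also reports earlier results by organism: "for bacteria, the sensitivity was 86.5% (95% CI 79.5%, 91.8%) when PCR was performed", and a norovirus study that "found a sensitivity of rectal swabs that was greater than 97" per cent. It cites one further study, of viruses and bacteria in children, that found no significant difference in detection for any agent. It gives no sensitivity for protozoa.

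**The concern.** The claim is made for every class, but the primary measures pool over classes. Pooled sensitivity is a weighted average whose weights are the shares of each class among the positives, and those shares depend on where participants are recruited. If the classes differ, as two of the cited studies suggest, a favourable pooled figure can coexist with clearly lower sensitivity in one class.

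The class-level analyses could guard against this, but the protocol does not say what they do to the conclusion. It does not say whether a class must reach 73 positives before a claim is made for it, whether recruitment is steered towards that number, or what follows if a class falls short. As written, an all-organism replacement claim could rest on a figure set by the recruitment mix.

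**Working it through.** **Inputs from the protocol.** Bacterial PCR sensitivity 86.5% and norovirus above 97% (Introduction). Planning sensitivity 95%; prevalence 20%, 25% and 30%; 61 and 92 pairs; 73 positives per pathogen subgroup; fewer than 600 samples (Sample size calculation).

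**Assumptions.** 97% is applied to all viruses. The bacterial share of positives is varied from 10% to 40%, because no expected mix is given.

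**1. The plan's own figures.** The precision formula is n = z² × Se × (1 − Se) / (d² × prevalence), with z = 1.96 and Se = 0.95, so the numerator is 3.8416 × 0.0475 = 0.1825. The half-width d is not stated in the text and is back-solved here.
- d = 0.10, prevalence 30%: 0.1825 / 0.0030 = 60.8, so 61.
- d = 0.10, prevalence 20%: 0.1825 / 0.0020 = 91.2, so 92.
- d = 0.05, positives only: 0.1825 / 0.0025 = 72.99, so 73.

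All three reproduce. The value 73 is also the total number of pairs at d = 0.10 and 25% prevalence. Its label as positives therefore fits only if d = 0.05.

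**2. Pooled sensitivity.** Pooled = (1 − b) × 0.97 + b × 0.865, where b is the bacterial share of positives.
- b = 10%: 0.8730 + 0.0865 = 0.9595 (96.0%)
- b = 20%: 0.7760 + 0.1730 = 0.9490 (94.9%)
- b = 40%: 0.5820 + 0.3460 = 0.9280 (92.8%)

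The pooled value is 95.0% when the viral share is (0.95 − 0.865) / (0.97 − 0.865) = 81%. If viral sensitivity were 98%, 99% or 100%, that share would be 74%, 68% or 63%.

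**3. What the bacterial stratum would show.** 600 pairs at 25% prevalence give 150 positives. At a 20% bacterial share, 30 are bacterial, and 0.865 × 30 is about 26. For 26/30 the 95% interval is 70% to 95% (Wilson) or 69% to 96% (exact). With 73 bacterial positives, 63/73 has an exact interval of 76% to 93%. With a true value of 86.5%, the exact upper limit falls below 95% in about 38% of trials with 30 bacterial positives and about 67% with 73.

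A two-sided Fisher test at 0.05 comparing 30 bacterial with 120 viral positives (86.5% versus 97%) has power of about 0.50.

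**4. Whether the 73 can be met by class.** Three classes need 3 × 73 = 219 positives, taking an even split with each positive pair counted in one class:
- 30% prevalence: 219 / 0.30 = 730 pairs
- 25%: 219 / 0.25 = 876 pairs
- 20%: 219 / 0.20 = 1,095 pairs

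Two classes need 146 positives: 487, 584 and 730 pairs. An uneven mix raises the need: at a 20% bacterial share, 73 bacterial positives imply 365 positives, or 1,460 pairs at 25% prevalence.

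**The case against.** The strongest reply is that the protocol already provides for organism differences. It plans stratified analyses for exactly this reason, states a minimum of 73 positives per pathogen subgroup, and promises 95% confidence intervals for all estimates. A reader might infer that poor bacterial performance would be hidden. The documents do not support that: the class result would be reported, and at 73 positives a typical result would exclude 95%. What remains is that nothing links the minimum to recruitment or to the conclusion, and that it is out of reach for three classes within 600 pairs at the stated prevalences.

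Other stronger readings also fail:
- **That the sample will be mainly viral.** Norovirus and hepatitis A clusters are named in the Abstract, but foodborne outbreaks, chronic carriers, GP and emergency presentations and inpatients are eligible too. No mix is stated.
- **That swabs miss more protozoa.** The protocol gives no protozoan sensitivity.
- **That bacteria would fail a protocol threshold.** 95% is a planning value, not a success criterion, and the interim margins are on accuracy, not sensitivity.
- **That the background evidence all points one way.** One cited study found no significant difference for any agent, and the 97% is a lower figure for norovirus alone.

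Finally, the standing of subgroups is often left to the analysis plan, which is not shown. That holds for their detail. It does not cover the mismatch within this article between the breadth of the claim and the primary measures.

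**Conclusion.** The point stands in a limited form. The claim covers three organism classes, the primary tables and margins cover none in particular, and the class-level analyses and the minimum of 73 have no stated role in the conclusion or in recruitment. On the protocol's own sensitivities, a pooled result of 92.8% to 96.0% is compatible with 86.5% in bacteria. At 600 pairs the bacterial estimate could rest on about 30 positives, with an interval of about 70% to 95%.

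These sizes depend on the assumed bacterial share, on applying the norovirus figure to all viruses, and on 25% prevalence. The 730 to 1,095 pairs depend on reading the 73 by class and on counting each positive pair once; pairs positive for more than one class would lower them. The mismatch between claim and analysis depends on none of these. It should be corrected because correction changes what the trial may conclude at little cost.

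**What to change.** Amend four places:
- **Introduction (aim):** state that the validity and replacement conclusion is drawn separately for viral, bacterial and parasitic/protozoan organisms.
- **Primary outcomes:** base each conclusion on that class's own sensitivity and 95% confidence interval, and report the pooled figure as descriptive.
- **Statistical methods:** give the disease-type analysis that role, name all three classes, and state that a non-significant comparison between classes is not evidence that they behave alike.
- **Sample size calculation:** say that the minimum of 73 positives applies to each class, that a class below it is reported as inconclusive with no claim made, and that fewer than 600 pairs does not deliver 73 positives in all three classes at 20% to 30% prevalence.

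This uses analyses already planned and needs no new numerical sensitivity goal, which the protocol does not contain. The cost is a possibly narrower result: the trial may be able to claim validity for only one class. Covering all three would mean recruiting beyond 600 pairs. At the planned 3 to 6 swabs per week, two years (104 weeks) yields about 312 to 624, apart from any outbreak surges.

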#### Primary outcomes.

We will assess the sensitivity, specificity, positive and negative predictive value, and positive and negative agreement value, using 2x2 tables. The gold standard will be bulk faeces PCR testing. Sensitivity is the proportion of individuals with the disease who test positive with rectal swabs. We will assess the cycle threshold (CT) values using general linear models if the relationship is linear as expected and estimate the receiver operating curves and areas under the curve to assess for the potential to need differential CT value cutoffs. All results will be reported using 95% confidence intervals.

The R statistical suite will be used for all analyses and data visualisation. All estimates will be presented with 95% confidence intervals (CI). P-values <0.05 are deemed significant, and p-values <0.1 are considered trends.

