### Study setting

The study aims to recruit patients in the community (primary care or public health responses) and in public hospitals. The mode of collection will either be a self-collect rectal swab (done by the patient themselves) and bulk faeces sample or clinician collect rectal swab and bulk faeces sample within a clinical environment. The generalisability of this trial is supported by its relatively broad inclusion and exclusion criteria, which are designed to reflect routine clinical practice. Because the trial aims to evaluate the use of rectal swabs as an alternative to bulk faeces sampling, eligibility is not restricted (e.g., based on symptom presentation), allowing for the inclusion of participants with diverse clinical profiles. This inclusive approach will mimic routine clinical practice, and facilitate recruitment across a broad range of demographic, clinical, and socioeconomic backgrounds, enhancing the external validity of the findings. Vulnerable groups, such as comorbid or immunocompromised individuals, are identified in the recruitment phase and this data is recorded to be used in the analyses. The lower age limit of 18 years has been set due to ethical and regulatory considerations in recruiting children and performing rectal swabs on a vulnerable group. While children are not included in this study, the trial findings relevant to rectal swab accuracy are expected to be applicable to all ages.

Inclusion criteria:

Persons aged 18 and older.Able to consent to and perform the additional rectal swab test.Close contact or person exposed, suspected, or confirmed case associated with an outbreak of an enteric organism. E.g., hepatitis A outbreak, foodborne outbreak.Chronic carrier of an enteric organism that requires testing.Person involved in a clinical encounter where they are or are likely suffering from a disease caused by an enteric organism. (E.g., person presenting to the GP or Emergency Department with diarrhoea or jaundice)

Exclusion criteria:

Persons unlikely (as judged by the clinician) to be harbouring an enteric organism.Persons where collection of a rectal swab is medically contra-indicated.

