### Outcomes

Primary Outcomes: Assess sensitivity, specificity, positive and negative predictive value, positive and negative agreement, accuracy, and receiver operating curves (at various CT value cutoffs), to determine the efficacy the new rectal swab approach.

Secondary outcomes: Acceptability of the rectal swabs in comparison to the gold standard of bulk faeces testing. This will be measured by asking participants which sampling method they preferred, and collecting information from participants in relation to any adverse events that may have occurred.

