**Fig 2 pone.0329643.g002:**
[figure not shown]
Sample size analysis. Includes a range of parameters. The “Sensitivity priors” represents the approximate expected sensitivity of our method, and the “proportion positive” represents the proportion of samples that will contain an organism, which also means that should test positive.

Constrained resources (e.g., funding), demands a higher pre-test probability at the time of testing to estimate with confidence. For example, if we only have funding for 40 persons tested, we will elect to test persons with clear known linkages to a person with the illness (symptomatic family member of someone diagnosed with norovirus), or we would perform clearance testing in persons with known disease using these methods (the guidelines call for clearance testing for a variety of illnesses). With greater funding, testing can approximate normal clinical encounters and have less restrictive criteria for testing. If the funding is limited to 40 samples, we will endeavour to control the testing method, aiming for in-clinic self-testing.

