### Recruitment

The recruitment strategy will be multifaceted to obtain samples from a range of representative clinical settings, e.g., outbreaks, community, and in-hospital. The strategy will involve a central study coordinator supporting acquisition of samples, coordinating the multiple sources. For outbreaks, the study coordinator will be able to send sample collection packs to the patient, family, and/or symptomatic members of an outbreak via express post. In community settings, the study coordinator can obtain samples from GP practices that are seeing patients who were recently inpatients in hospital – identified from admission lists, or our Infectious Diseases Physician study collaborators. Inpatients, especially those which represent persons with a high pre-test probability, will be identified, recruited via their treating practitioner, and then consented to take part in the study. Consent will be performed verbally over the phone by a study coordinator (records kept locally), and/or with a physical form sent in a return envelope.

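### PPV and NPV are primary outcomes taken from 2x2 tables, but recruitment and funding set the positive proportion, so the crude values may not describe routine practice

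*Protocol article*

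**What the plan says.** The Outcomes section lists predictive values among the primary outcomes: "Assess sensitivity, specificity, positive and negative predictive value, positive and negative agreement, accuracy, and receiver operating curves". The Primary outcomes part of Statistical methods gives the method: "We will assess the sensitivity, specificity, positive and negative predictive value, and positive and negative agreement value, using 2x2 tables". Bulk faeces PCR is the reference, and "All results will be reported using 95% confidence intervals".

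Three places bear on who will be in those tables.

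- Recruitment covers outbreaks, the community and hospital, and says: "Inpatients, especially those which represent persons with a high pre-test probability, will be identified".
- The paragraph below Fig 2, in Sample size calculation, ties the case mix to money. With funding for only 40 persons, the trial would choose people clearly linked to a diagnosed case, or "we would perform clearance testing in persons with known disease using these methods". With more funding, testing is said to be able to come close to ordinary clinical encounters.
- Study setting describes the eligibility criteria as broad and states without condition: "This inclusive approach will mimic routine clinical practice".

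The Introduction gives the aim as replacing bulk faeces testing in daily clinical and public health practice. Planned stratification is by pathogen (Sample size calculation) and by disease type (Statistical methods). The accuracy regression lists sex, age, collector, comorbidities, symptom status, symptom duration and blood in the sample. Setting is recorded (Data collection and management), and testing location is an adjuster for adverse-event severity (Secondary outcomes). Neither setting nor recruitment route is a listed covariate or subgroup for accuracy.

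**The concern.** Sensitivity and specificity condition on the reference result and do not depend algebraically on how many participants are positive. PPV and NPV condition on the swab result and do. If the share of positives is raised by design, PPV goes up and NPV goes down with no change in the swab.

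Under this protocol, two of the primary figures would therefore change with the recruitment mix, and that mix is partly a function of budget. A clinician would use NPV to decide whether a negative swab can be relied on, and an outbreak team would use PPV when screening contacts. Because Study setting says the sample resembles routine practice, readers are invited to carry the crude values straight into that use.

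**Working it through.** **1. The protocol's own figures.** Sample size calculation gives a planning prevalence ("Assuming that 30% of samples will contain an organism") and a sensitivity ("with an expected sensitivity of at least 95" per cent). The usual precision formula for sensitivity is n = z² × Se(1 − Se) / (d² × p), with z = 1.96. The half-width d is not stated in the text. Taking d = 0.10:

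- p = 0.30: 3.8415 × 0.0475 / (0.01 × 0.30) = 60.8, rounded up to 61, as stated.
- p = 0.20: 3.8415 × 0.0475 / (0.01 × 0.20) = 91.2, rounded up to 92, as stated.

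With d = 0.05, the positives needed are 3.8415 × 0.0475 / 0.0025 = 72.99, rounded up to 73, as stated per pathogen subgroup. These figures are not in dispute. They are precision targets for sensitivity and say nothing about PPV or NPV.

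**2. What 40 samples imply.** By the same formula with d = 0.10, 18.25 positives are needed. With 40 pairs that means 18.25 / 40 = 46% positive, well above the roughly 25% that the protocol takes from the literature. This fits the protocol's own statement that tight resources call for a higher pre-test probability.

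**3. Predictive values by Bayes' rule.**

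PPV = Se·p / [Se·p + (1 − Sp)(1 − p)]

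NPV = Sp(1 − p) / [Sp(1 − p) + (1 − Se)p]

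Se = 0.95 is the protocol's planning value. The protocol gives no specificity, so Sp = 0.98 is assumed. Prevalences of 20%, 25% and 30% are the protocol's; 46% comes from step 2; 60% is an assumed enriched value.

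| Prevalence | PPV | NPV |
|---|---|---|
| 20% | 0.190/0.206 = 92.2% | 0.784/0.794 = 98.7% |
| 25% | 0.2375/0.2525 = 94.1% | 0.735/0.7475 = 98.3% |
| 30% | 0.285/0.299 = 95.3% | 0.686/0.701 = 97.9% |
| 46% | 97.6% | 95.9% |
| 60% (assumed) | 0.570/0.578 = 98.6% | 0.392/0.422 = 92.9% |

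From 25% to 60%, NPV falls by 5.4 points and PPV rises by 4.5. The share of swab-negative people who are positive on bulk faeces goes from 1.7% to 7.1%. From 20% to 30%, PPV rises by 3.1 points and NPV falls by 0.8.

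**4. Dependence on the assumed specificity (Se 0.95, 25% against 60%).**

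| Sp | PPV | NPV |
|---|---|---|
| 0.90 | 76.0% to 93.4% | 98.2% to 92.3% |
| 0.95 | 86.4% to 96.6% | 98.3% to 92.7% |
| 0.99 | 96.9% to 99.3% | 98.3% to 93.0% |

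The fall in NPV hardly depends on specificity. The rise in PPV depends on it strongly, from 2.4 points at Sp 0.99 to 17.4 at Sp 0.90.

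**The case against.** The strongest reply is that splitting results by route and standardising to a target prevalence are commonly left to a statistical analysis plan, which is not shown here and which the Oversight section expects statisticians to write. Nothing in the protocol forbids it. Sensitivity and specificity will be reported with intervals, so predictive values at any prevalence can be worked out later. No stated decision depends on PPV or NPV: sample size rests on sensitivity, and the interim rules on a difference in accuracy. The regression on symptom status and duration also captures part of the case mix.

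Most of this is fair and limits the seriousness of the point. It does not remove it. The protocol does state a method for two primary outcomes, and the listed covariates do not turn crude PPV and NPV into values for another population. The unconditional claim in Study setting also conflicts with the funding paragraph, whatever an analysis plan adds.

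A reader might infer several stronger things that the text does not support:

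- **That PPV and NPV will not describe routine practice.** That is firm only in the 40-person contingency. The protocol also contemplates up to about 600 samples, seeks representative settings, and says more funding would bring testing close to ordinary encounters.
- **That one pooled table is planned.** The text says tables, in the plural, with pathogen and disease-type splits. The narrower point is that none of the stated splits separates enriched from routine participants.
- **That the distortion could reach 27 points in PPV** (98.6% at 60% against 71.4% at 5%, with Sp 0.98). Both prevalences are assumed, and people judged unlikely to harbour an organism are excluded.
- **That clearance or known-disease pairs should be dropped.** Carriers who require testing are eligible, and the protocol notes that guidelines call for clearance testing. Such people may or may not still be positive, so their paired result is not known in advance.

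**Conclusion.** The point holds as a weakness in how two primary outcomes are to be estimated and read. Crude PPV and NPV will track the recruitment mix, and no planned split or listed accuracy covariate separates that mix by route or setting. They may therefore misdescribe routine use.

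The size depends on the final mix. It is small if the proportion positive stays within the protocol's 20% to 30%. It is about 5 points in each of PPV and NPV at an assumed 60%, given Se 95% and Sp 98%. Specificity and the enriched prevalence are assumptions, and the half-width in the sample size formula is inferred from the figures it reproduces. Sensitivity and specificity are not affected by this algebra, although they too may differ between recruitment routes. The change should be made, but the point does not threaten the validity of the trial.

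**What to change.** - Report sensitivity and specificity by recruitment route (outbreak contact or case, carrier or clearance testing, symptomatic presentation) and by setting.
- Derive PPV and NPV from them by Bayes' rule at prevalences fixed in advance: the protocol's 20%, 25% and 30%, plus a lower screening value such as 5%, declared as an assumption. Give 95% intervals by bootstrap or the delta method.
- Label any PPV or NPV read directly from a 2x2 table as applying to the study sample only.
- Keep clearance and known-disease pairs, and report them as their own stratum.
- Reword the representativeness claim in Study setting so that it agrees with the funding paragraph below Fig 2 and with Recruitment.

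The cost is a few more lines of analysis and one recruitment-route flag. Setting is already collected, but route is not in the listed minimum data. No further participants or samples are needed. The drawback is wider intervals within strata, especially if the total is small.

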#### Decision rules.

Stopping for Safety: Predefined criteria for stopping the trial if a significant safety concern are identified; for instance, if the incidence of severe adverse events is above what is expected.Stopping for Efficacy: Criteria for stopping the trial early if rectal swabs show clear and overwhelming evidence of inferiority, based on predefined statistical thresholds and thus it is futile to continue. A cutoff of 0.35 difference in accuracy for inferiority with an alpha of 0.05 at interim analyses will be used to support decisions on continuing, modifying, or stopping the trial. As this is a diagnostic test trial, the decision to stop the trial must be multifactorial in nature and made by the Trial Steering Committee.

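### Labelling p-values below 0.1 as trends undermines the promised control of type I error in the covariate, subgroup and secondary tests

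*Protocol article*

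**What the plan says.** The general part of Statistical methods describes group comparisons by chi-square and t-tests and then states: "We will also adjust for multiple comparisons to control for type I error". It names neither the method of adjustment nor the family of tests. The next paragraph introduces logistic regression models and lists seven variables as possible confounders: the participant's sex and age group, who took the swab, comorbidities, whether symptoms were present and for how long, and visible blood. It adds: "Subgroup analysis will be conducted according to disease type (e.g., viral, or bacterial".

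The subsection Primary outcomes fixes two thresholds: "P-values <0.05 are deemed significant, and p-values <0.1 are considered trends". It does not say whether they apply to raw or adjusted p-values, and it does not confine the trend label to exploratory work. The paragraph opens by naming the software for every analysis, so its wording is not limited to the primary outcomes. The same paragraph says: "All estimates will be presented with 95% confidence intervals (CI".

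**The concern.** Multiplicity control exists to limit how many chance results are presented as findings. A second tier fixed in advance at 0.1 pulls the other way: it gives a positive name to results that failed the trial's own criterion, at twice the nominal per-test error rate.

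It also fits poorly with the reporting standard in the same paragraph. A two-sided p-value between 0.05 and 0.10 normally goes with a 95% confidence interval that includes no effect, yet the text would call that result a trend.

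What is at stake is the reading of tests on who collected the swab, symptom status, disease type and adverse events. The Introduction says the intended outcome is to replace bulk faeces testing in daily practice, so a remark that accuracy tended to differ by type of collection could carry weight that the data do not support.

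**Working it through.** **Inputs**
- Thresholds 0.05 and 0.10: Primary outcomes.
- Seven covariates (sex, age group, collector, comorbidities, symptomatology, duration of symptoms, blood in the sample): Statistical methods.
- Assumptions not in the article: one test per covariate, independent tests, no true effects, and Bonferroni as the example of an adjustment. The number of disease-type subgroups is not given, so 1 to 7 further tests are added to show a range.

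**Step 1. Do the plan's own figures depend on the trend rule?** Sample size calculation gives 61 paired samples ("means we will require a sample size of no more than 61 paired samples"), 92 at 20% prevalence, and 73 positives per pathogen subgroup. The precision formula is n = 1.96² × Se(1 − Se) / (d² × prevalence), with Se = 0.95. The half-width d is not in the text; the values below are inferred because they reproduce the figures.
- d = 0.10, prevalence 0.30: 60.8, rounded up to 61.
- d = 0.10, prevalence 0.20: 91.2, rounded up to 92.
- d = 0.05, positives only: 73.0, so 73.

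All three figures are reproduced from a two-sided 95% interval. None uses a 0.1 threshold.

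**Step 2. Thresholds applied to raw p-values, seven tests.** The chance of at least one flag is 1 − (1 − α)^7.
- p < 0.05: 1 − 0.95^7 = 30.2%.
- p < 0.10: 1 − 0.90^7 = 52.2%.
- Expected number of flags: 7 × 0.05 = 0.35 against 7 × 0.10 = 0.70.

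The 52.2% includes results below 0.05. The part due to the trend clause alone, meaning at least one trend and nothing significant, is 52.2 − 30.2 = 22.0 percentage points.

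**Step 3. Thresholds applied to Bonferroni-adjusted p-values, seven tests.** The chance is 1 − (1 − α/7)^7.
- Adjusted p < 0.05: 1 − (1 − 0.05/7)^7 = 4.9%.
- Adjusted p < 0.10: 1 − (1 − 0.10/7)^7 = 9.6%.

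**Step 4. Range when subgroup tests are added.**

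| Tests | Raw, 0.05 | Raw, 0.10 |
|---|---|---|
| 7 | 30.2% | 52.2% |
| 8 | 33.7% | 57.0% |
| 10 | 40.1% | 65.1% |
| 14 | 51.2% | 77.1% |

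On Bonferroni-adjusted p-values the rates barely move over this range: about 4.9% at 0.05 and 9.5% to 9.6% at 0.10.

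**Step 5. Ratio.** With seven tests the trend tier multiplies the chance of a flagged null result by 52.2/30.2 = 1.7 on raw p-values, and by 9.6/4.9, about 2, on adjusted ones.

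**The case against.** The strongest reply is that nothing here is an error. One can adjust the p-values, compare them with 0.05, and give a separate name to the band from 0.05 to 0.10. The error rate of any claim called significant is then unchanged. That stands. A reader might infer that the two sentences contradict each other, but the documents do not support it: the article never calls its thresholds unadjusted, and both sentences can be obeyed.

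A reader might also set 52% against 5% as the cost of the clause. That comparison changes two things at once, the threshold and the adjustment. On raw p-values, 30% is already present without the trend tier. The like-for-like contrasts are 30% to 52%, or 4.9% to 9.6%.

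The seven-test family is also a construction. The article names the covariates as potential confounders and does not say that each p-value will be tested or labelled. Age groups and comorbidities may need several terms, and the promise of adjustment sits next to the simple group comparisons rather than the regression models. The figures are therefore illustrative. Which tests form the family, and by what method they are adjusted, may properly be left to an analysis plan that is not shown; that silence is not criticised here.

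The reply does not defend the label itself. The clause is a rule that the article does fix, in general wording. On either reading of the thresholds it increases the number of chance results with a favourable name, and a later analysis plan would have to depart from the published text to remove it.

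**Conclusion.** The trend clause undermines the stated aim of controlling type I error without strictly contradicting it. For seven independent null tests, one per listed covariate, the chance of at least one result flagged as a trend or better goes from 30% to 52% on raw p-values, or from 4.9% to 9.6% on Bonferroni-adjusted ones. The article does not settle which case applies.

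The reach is limited. A reader might infer that the trial's main conclusions or its stopping rule are compromised; the text does not support that. The main accuracy measures are reported as estimates with 95% confidence intervals. The sample sizes rest on interval precision. The interim rule under Decision rules has its own threshold ("A cutoff of 0.35 difference in accuracy for inferiority with an alpha of 0.05 at interim analyses") and does not use the label. Nor does the article say that trends will appear in its conclusions. This is a minor improvement to how covariate, subgroup and secondary tests are read.

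**What to change.** In Primary outcomes, delete the clause "p-values <0.1 are considered trends" and its linking word. State that the 0.05 threshold applies to the multiplicity-adjusted p-values promised under Statistical methods. Report all other comparisons as estimates with 95% confidence intervals, without significance or trend labels.

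The cost is about one sentence of editing and fewer labelled findings. No data or power are lost: borderline results remain visible through their estimates and intervals, and only the label goes.
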